### Participant information sheets

Participant Information Sheets were approved by the Research Ethics Committee (REC), and provide an overview of the study for potential participants. Researchers are also on hand to explain the information contained in the information sheet and to ensure fully informed consent, documented with signed consent forms. Participants are not deceived in any way. Readability of information sheets was also considered and assessed using the SMOG Grading index
[25]. The SMOG was calculated using an online calculator developed by its author (http://www.harrymclaughlin.com/SMOG.htm) and can generate equivalent grade levels for comprehension, which can also be categorised in line with the United States Department of Health and Human Services (USDHHS) standards (for example,
[26]). SMOG levels and equivalent classifications and school ages for the participant materials used in the present study are reported in Table 
1.

**Table 1 T1:** Readability estimates for participant information sheets

**Material**	**SMOG score**	**USDHHS classification**	**British school age equivalent**
**Participant information sheet**	10.27	Difficult	15 to 17 years
**Consent form**	10.19	Difficult	15 to 17 years
**Email security information sheet**	9.24	Average	12 to 15 years

### Interventions

All eligible patients are offered participation in the trial following a team discussion within the Eating Disorders Service (EDS) and are then randomly assigned to one of the three conditions. This involves meeting with one member of the research team who will go through the trial protocol and information sheets. This is not the patient’s individual clinician, but the appointment can potentially occur directly before or after a planned appointment if this is more convenient for the participant. This helps ensure completion of questionnaires and enables the participant to ask any questions directly relating to the trial. If individuals decide not to participate in the trial, they are offered treatment as usual.

Both GSH interventions are based on a self-help treatment
[20,27] that has documented efficacy, and a copy of the book is provided to patients. The treatment is “program-led”
[28]; that is, the aim of the therapist is to support the patient in adhering to the principles of the book, and thus does not require extensive clinical training. The treatment is designed so that non-specialist therapists can readily administer this intervention
[29].

### Face-to-face GSH

This treatment follows the self-help manual, *Overcoming Binge Eating*[20,27], and provides 10 sessions of face-to-face therapist care, with each session lasting 20 to 25 minutes. The first session may last longer than this, due to a need to review since the patient was last seen at the EDS and to allow the patient more time to socialise to treatment (see
[28]). Guidance for the provision of GSH has been provided in Fairburn
[28], and 10 sessions are provided over a period of 12 weeks. There is no specific guidance about the frequency of sessions, although the initial sessions are recommended to be at least weekly with the remaining sessions being adapted to suit the patient’s progress
[28]. A typical format might be to have the first eight sessions weekly, with the remaining two occurring over the following month (that is, fortnightly).

The second edition of the book in particular
[27] might be considered as ‘multicomponent GSH’ as it has been based on Cognitive Behaviour Therapy-Enhanced (CBT-E)
[30] and designed to address many core elements of an eating disorder, including topics such as self-monitoring, psychoeducation and regular weighing. The support provided in this RCT is, adopting the taxonomy suggested by Glasgow and Rosen
[31], likely to fall somewhere between ‘therapist-administered’ and ‘minimal contact’. A more recent paper
[32] has elaborated further on this taxonomy, suggesting that the form of GSH used here is best described as ‘minimal contact therapy’ as opposed to ‘therapist-administered’, the latter being where self-help material “augments the impact of a standard therapy” (p. 90,). The recent review of Farrand and Woodford
[33] found a lack of studies adopting this taxonomy, although the definition suggested by Glasgow and Rosen
[31] (and the more updated modifications from Newman *et al*.
[32]) might be difficult to determine *a priori*. Many evaluations of self-help treatment have considered both of these categories together under the wider umbrella of ‘GSH’ and, while the lack of definition regarding the degree of involvement from professionals is a shortcoming of the existing literature
[33], it is hoped that a retrospective assessment of this can be made in the current study. It would be interesting to look at the content of GSH sessions retrospectively to consider the degree of support (that is, ‘therapist-administered’ or ‘minimal contact’) as a possible moderator of outcome. In terms of treatment in the current study, GSH was devised by the developer to involve a therapist, but to a lesser degree than in conventional CBT (see
[28]). The treatment was designed to be used by non-specialist therapists who help the patient follow the GSH programme
[29] by providing support, encouragement and monitoring of progress. Therapists also discuss goals and elements of the programme identified by patients as those that they wish to raise (for example, parts they donot understand, disagree with or parts that are not especially relevant), as well as potential solutions.

Of note, the term ‘therapist’ is used here to refer to those individuals on the ‘professional side’ of the patient-therapist dyad. However, some authors (for example,
[34,35]) have argued that use of this term in self-help could set up certain expectations about the treatment that might hamper progress; thus, terms such as ‘guide’ and ‘facilitator’ have alternatively been used. As in other treatments and manuals the precise term used could be modified to suit the individual setting (for example, see
[36]).

### Email supported GSH

This treatment involves patient-therapist contact via e-mail. Patients are advised to follow the treatment closely (which is divided into ‘steps’) and instructed to contact the therapist at least once a week, and can receive feedback up to twice a week for a period of 12 weeks
[19]. Email is the preferred medium for all communication, with face-to-face and telephone appointments occurring at a minimum. The one exception to this is that the first appointment is always conducted in person so that the patient can meet their therapist, receive a copy of the manual, be weighed at the clinic and so on. As sparse guidance exists on how best to implement email supported GSH, the treatment has been conceived firstly to parallel the face-to-face condition (see above); for example, contact is less frequent towards the end of the sessions. We have, secondly, followed the methodology of Ljotsson *et al*.
[19] as this was the first example of providing GSH with the current manual with email support. Participants could (although this is not an exclusive list): get feedback on homework and progress; ask questions; and receive guidance regarding the self-help program. A more recent study
[12] has described a similar intervention, although less detail is reported on the exact nature of support. The focus of supervision and the practice of treatment were to follow the guidelines of the therapist’s manual
[28]. In the current study, therapists are advised to follow similar guidelines to the face-to-face condition. For example, therapists will still aim to discuss problems, identify solutions and monitor progress; the treatment is proposed to be delivered in a similar manner, but via the medium of email. The focus in both treatment conditions is on the eating disorder, and therapists may only address other issues if they are of “immediate relevance to the binge eating problem” (
[28], p. 9). Email can be sent securely by both patient and therapist although patients will have to agree to download a software package from Cisco and create a password (this is optional, although it enhances data security). Identification of any significant increased risk (for example, medical, suicidal) would prompt a telephone call or face-to-face meeting from the therapist.

### Delayed treatment condition

The delayed treatment condition lasts 12 weeks, and data obtained from this period serve as waiting list control conditions. As at other stages of treatment, if, at review, participants wish to opt out of the study they will receive treatment as usual. There is no six-month follow-up for this condition.

### Primary and secondary outcomes

The primary outcome will be frequency of objective bulimic episodes, as assessed by the Eating Disorder Examination Questionnaire (EDE-Q) (see below). Comparisons will be made between pre-treatment, post-treatment and follow-up in the intervention groups. Secondary outcome measures include overall eating psychopathology, other ED behaviours, such as self-induced vomiting, psychological distress, self-esteem, functional impairment and healthcare usage, assessed by self-report (see below). Some of these variables (for example, severity of ED psychopathology) will be considered as predictors of outcome, as well as considered aspossible mediating or moderating variables, such as therapeutic alliance or type of therapeutic support.

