### Objectives and hypotheses of the RCT

The overall aim of the trial is to evaluate whether therapist support within GSH can be as effective when delivered via email as when delivered face-to-face. In this paper, we detail the design and methods of the current trial, and clarify the four main aims of the study. Specifically, these are to: (1) compare the effectiveness of face-to-face versus email GSH during treatment and at follow-up; (2) determine relative attrition and drop-out across the two treatments; (3) look at predictors of outcome in GSH (see below); and (4) determine the relative cost-effectiveness of these two treatments. The study also employs a waiting list control condition. The current paper describes the protocol on which the clinical trial is based, in line with suggested guidance (for example,
[23]).

In terms of the primary outcome measure, it is expected that both treatment conditions will be superior to the waiting list control condition (for example,
[4,18]). Although there is a limited amount of evidence in eating disorders, it is hypothesised that both treatments (face-to-face and email GSH) will be comparable in terms of effectiveness (for example,
[24]) in reducing binge eating frequency (see also
[21]). It is expected that similar results will be found with secondary outcome measures, drop-out and cost-effectiveness, although these variables have not yet been studied in detail in this way.

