### Data collection

Data from the EDE-Q provide the primary outcome variable - binge eating frequency. Secondary variables include compensatory behaviours (for example, self-induced vomiting), and ED psychopathology, as well as constructs assessed by the other measures (self-esteem, psychological distress, functional impairment). Weight and BMI are not outcome variables, but may be included in analyses, for example, to give demographic information or as covariates. Other routine demographic information (for example, ethnicity) will also be recorded. Participants are asked to complete self-report measures (mailed or otherwise given by hand) at start-of-treatment, end-of-treatment and six-month follow-up (with the exception of the HAq-II; see Table 
2). Data will be stored on a secure computer server and analysed with computer statistics software (for example, SPSS **IBM Corporation, Armonk, NY, USA**). Oxford is the lead site for data coordination. In order to promote data quality, data will be examined for impossible values and a sample of electronic data (around 10%) will be double-checked by another researcher with raw data. Blinding is not used in this study, and so an emphasis on appropriate outcome measurement and allocation concealment is crucial
[50,51].

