### Statistical methods

Regarding the primary aim - comparing active treatment and control condition - results will be analysed using analysis of variance and *t*-tests. Effect sizes will also be assessed, and expressed appropriately (for example, Cohen’s *d*). Logistic regression analyses will look at predictors of outcome, and potential mediators and moderators might also be considered. However, a number of existing studies addressing this issue have been underpowered
[33] so this remains an important consideration. Differences in outcome variables will be analysed (for example, through χ^2^, regression) to examine attrition/drop-out. In terms of cost-effectiveness, analyses will be conducted based on data obtained through the health utilisation questionnaire, therapist time questionnaire and measures of functional impairment (CIA) and ED symptoms (EDE-Q).

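### The primary analysis names ANOVA and t-tests with no baseline term, and the outcomes section and the statistical section do not set out the same comparison

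*Protocol article*

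**What the plan says.** - **Outcome.** Primary and secondary outcomes: "The primary outcome will be frequency of objective bulimic episodes, as assessed by the Eating Disorder Examination Questionnaire (EDE-Q"). Data collection repeats it: "Data from the EDE-Q provide the primary outcome variable - binge eating frequency".
- **Comparisons listed with that outcome.** The next sentence of Primary and secondary outcomes reads: "Comparisons will be made between pre-treatment, post-treatment and follow-up in the intervention groups". The waiting list is not mentioned.
- **Tests.** Statistical methods, on the primary aim: "comparing active treatment and control condition - results will be analysed using analysis of variance and *t*-tests". Effect sizes such as Cohen's d are added. No baseline term or count model is named, and the type of ANOVA is not given.
- **Baseline.** Data collection: "Participants are asked to complete self-report measures (mailed or otherwise given by hand) at start-of-treatment, end-of-treatment and six-month follow-up". Table 2 confirms a baseline EDE-Q.
- **Covariates.** Only weight and BMI are mentioned, as options: "Weight and BMI are not outcome variables, but may be included in analyses, for example, to give demographic information or as covariates".
- **Hypotheses.** Objectives and hypotheses: "it is expected that both treatment conditions will be superior to the waiting list control condition". The same section makes email against face-to-face the overall aim.
- **Waiting list.** Delayed treatment condition: this arm lasts 12 weeks and has no six-month follow-up.

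**The concern.** There are two linked difficulties.

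First, the comparison is not stated consistently. The outcomes section describes change over time in the treated arms, the statistical section describes active treatment against control, and the objectives give email against face-to-face as the overall aim. No test is explicitly attached to that last contrast. If the outcomes sentence were carried out as before-after tests in each treated arm, the results would mix treatment effect with regression to the mean and natural course, because participants enter on account of regular binge eating. Such results could not support a claim against control or between the treatments.

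Second, the named tests leave a measured baseline of the primary outcome unused, or use it inefficiently. With a floor of 17 per group, and a sample size section that worries openly about low power, this is an avoidable loss. Episode frequency is also a non-negative quantity that may be skewed, in which case a raw-mean t-test gives up further power.

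**Working it through.** **1. The plan's own figure.** Inputs from Sample size: two-sided alpha 0.05, d = 1.0, power 0.80. The noncentral two-sample t gives 16.71 per group, rounded up to 17; power at 17 is 0.807. Three groups give 51, and 51/(1 − 0.50) = 102. The plan's figures reproduce, and they correspond to an unadjusted two-group t-test.

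**2. What the named tests can mean.** Let r be the correlation between baseline and 12-week outcome, with equal variances. Relative to the outcome variance, the variance factors are:

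- t-test or one-way ANOVA on post-treatment scores: 1
- group-by-time ANOVA with one pre and one post value, which is the t-test on change: 2(1 − r)
- baseline-adjusted model (ANCOVA): 1 − r²

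Since 1 − r² = (1 − r)(1 + r) and 1 + r ≤ 2, the adjusted factor is never larger than either of the others. The price is one degree of freedom.

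**3. Size on the normal scale.** The article gives no r, so 0.3, 0.5 and 0.7 are assumed. The adjusted factors are 0.91, 0.75 and 0.51, so the unadjusted test needs 1/0.91 = 1.10, 1/0.75 = 1.33 and 1/0.51 = 1.96 times the adjusted sample. Power uses noncentrality d/√factor × √(n/2), with 2n − 2 degrees of freedom (2n − 3 for ANCOVA).

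| n per group, d | Analysis | r = 0.3 | r = 0.5 | r = 0.7 |
|---|---|---|---|---|
| 17, 1.0 | post score | 0.81 | 0.81 | 0.81 |
| 17, 1.0 | change score | 0.67 | 0.81 | 0.95 |
| 17, 1.0 | baseline-adjusted | 0.84 | 0.90 | 0.98 |
| 44, 0.54 | post score | 0.71 | 0.71 | 0.71 |
| 44, 0.54 | change score | 0.56 | 0.71 | 0.90 |
| 44, 0.54 | baseline-adjusted | 0.75 | 0.82 | 0.94 |

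Both effect sizes and both group sizes come from Sample size (0.54 is the cited review estimate, 44 the ideal number). At 0.54 and 44 per group the post-score test falls short of 0.80; adjustment reaches it if r is about 0.5 or more.

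**4. Possible skewness.** The article gives no mean, dispersion or rate ratio for episodes. A simulation therefore assumed lognormal-Poisson counts with mean 16, log-rate SD 0.8 to 1.0, log-rate correlation 0.4 to 0.7 and a rate ratio of 0.5 (2,000 runs per setting). Power ranges:

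| Analysis | 17 per group | 44 per group |
|---|---|---|
| t-test, post | 0.32–0.51 | 0.70–0.91 |
| t-test, change | 0.19–0.45 | 0.40–0.82 |
| ANCOVA, raw count | 0.34–0.69 | 0.73–0.98 |
| ANCOVA, log(count + 1) | 0.45–0.76 | 0.86–0.99 |

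With no treatment effect, the post-score t-test rejected in 0.033 to 0.054 of runs. Skewness cost power here and did not inflate the error rate.

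**5. A less favourable case.** Under a different assumed model (negative binomial counts, baseline mean 14, 17 per arm) with latent correlation 0.3, the post-score t-test had 45% power and the baseline-adjusted linear model 44%, so adjustment gained nothing. At 0.6 the figures were 48% and 61%. A quasi-Poisson model with log baseline reached about 69% to 70% at 0.6, but its type I error was 6–7%; held to a true 5% it had about 65%.

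**The case against.** The strongest reply is that the randomised comparison is planned. Statistical methods names active treatment against control, and the objectives state between-arm hypotheses. The outcomes sentence does not say that the comparisons are within each group, and the missing six-month visit explains why only the intervention groups can be compared at all three times. This stands. A reader might infer from the outcomes sentence that the trial offers no randomised contrast on its primary outcome; the statistical section rules that out for active against control.

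Next, the absence of a baseline term is read from silence in a condensed article, and a repeated-measures ANOVA would use the baseline. This stands in part. The article does name its tests and its possible covariates, and baseline episode frequency is not among them. A group-by-time ANOVA with one pre and one post value is the change-score test, so it is still no more efficient than adjustment.

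Third, skewness, r and dispersion are assumptions, and the gain may be small. This stands, as does the point that 17 per group is a floor: at least 102 are to be recruited, which is 34 per arm before dropout. A particular count model is also a preference; ANCOVA on a log scale is equally defensible.

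**Conclusion.** The concern holds as one of efficiency and of inconsistent wording. The stated tests are valid, but a nearly free improvement is available, and the outcomes and statistical sections should describe the same contrasts, including email against face-to-face.

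The size depends on r, which the article does not give. Against the post-score test the gain is negligible to modest at 0.3 and substantial at 0.5 to 0.7. Those normal-scale figures assume equal variances before and after treatment; the count results rest on the simulated distributions.

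A reader might go further and conclude that the t-tests would give misleading P values on a skewed count. The simulations do not support that, with type I error of about 3–5%. Nor is the quasi-Poisson power of about 69% a like-for-like gain, since that test exceeded its nominal error rate.

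**What to change.** Align Primary and secondary outcomes with Statistical methods before outcome data are examined:

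- Define the primary analysis as the between-arm difference in objective bulimic episode frequency at 12 weeks, naming each treatment against waiting list and email against face-to-face.
- Adjust for baseline episode frequency.
- Use a model suited to a possibly skewed count. ANCOVA on log(count + 1) is one option. An overdispersed count model is another, with small-sample or permutation inference because the arms are small.
- Report within-group change descriptively.
- Report the six-month data as a secondary comparison of email with face-to-face.

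The cost is revised wording, slightly more analysis work and an effect measure (a ratio) less familiar than a mean difference or Cohen's d. No additional data or visits are required.

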### Assessments and timeline

All patients are assessed by the EDS following initial referral to the service. This is a full clinical assessment and will identify current symptoms as well as aspects related to comorbidity, risk and so on. For example, if patients indicate on self-report questionnaires that they are a risk to themselves or others, the clinician will discuss this further. If they are then eligible for, and consent to, the trial they meet with one of the research team to give written consent. The assessment procedure is outlined in Table 
2.

**Table 2 T2:** Schedule for assessment

**Measure**	**Baseline**	**Session 3**	**End-of-treatment (12 weeks)**	**Six-month follow-up**
** *Self-report* **				
**Demographics form**	X			
**Contact information**	X			
**EDE-Q**	X		X	X
**CORE-OM**	X		X	X
**RSES**	X		X	X
**CIA**	X		X	X
**Helping alliance questionnaire**		X	X	
**Healthcare usage questionnaire**	X		X	X
** *Completed by therapist* **				
**Weight/BMI**	X		X	X
**Therapist time questionnaire**			X	X
**Helping alliance questionnaire**		X	X	

BMI, body mass index; CIA, Clinical Impairment Assessment; CORE-OM, Clinical Outcomes in Routine Evaluation - Outcome Measure; EDE-Q, Eating Disorder Examination Questionnaire; RSES, Rosenberg Self-Esteem Scale.

Data from the following measures will be collected:

The EDE-Q v6.0;
[37] is a self-report questionnaire that assesses eating disorder symptoms and has good psychometric properties
[38]. Participants rate how frequently they have experienced symptoms (both attitudinal and behavioural) of an ED over the last month on a 0 to 6 scale (ranging from “no days” to “every day”).

The Clinical Outcomes in Routine Evaluation-Outcome Measure (CORE-OM;
[39]) is a self-report measure of general psychological distress. Thirty-four items assess symptoms over the preceding week and are rated on a five-point frequency scale (from “not at all” to “most or all of the time”), which can generate a global score indicating overall functioning. Its utility in eating disorders has been demonstrated
[40].

The Rosenberg Self-Esteem Scale (RSES;
[41]) comprises 10 items that measure global self-esteem. Responses are given on a four-point scale from 1 (“strongly agree”) to 4 (“strongly disagree”), with half of the items reverse-scored.

The Clinical Impairment Assessment (CIA;
[42]) is a 16-item self-report measure assessing psychosocial impairment resulting from ED symptoms. Participants are asked to consider the preceding 28 days and to indicate to what degree symptoms of an ED have affected different areas of their life. Responses range from “Not at all” to “A lot” (scored from 0 to 3), and a total score (0 to 48) can be calculated giving an overall indication of functional impairment. The CIA has demonstrated acceptable psychometric properties across a range of samples
[43].

The Helping Alliance questionnaire (HAq-II;
[44]) is a 19-item measure of therapeutic alliance, showing good psychometric properties. It comprises both positive and negative items (which are reverse-scored), and includes both a patient- and therapist-version. Statements regarding the therapeutic alliance are rated from 1 (“strongly disagree”) to 6 (“strongly agree”). A mean score is calculated by adding up all items (reverse-scoring as appropriate), calculating a mean, and then multiplying this by 19 (which should be identical to the total score if all items are completed). Thus, scores range from 19 to 114 (with higher scores indicating better alliance). It has the advantage of assessing alliance independent of symptom improvement and has been used in previous ED treatment studies (for example,
[45]).

In addition, a measure assessing healthcare use developed specifically for this study will be given (see Additional file
1). This will be administered with the standard pack of questionnaires (that is, at start-of-treatment, end-of-treatment and follow-up) for individuals who consent to the study. An estimate of cost effectiveness will be made by monitoring resource use directly associated with different treatment conditions (for example, therapist time spent providing care). The proportion of binge-free days (estimated through the EDE-Q) will also be used to estimate cost effectiveness (for example,
[46]). Therapist time will be estimated using a simple checklist of time spent engaged in treatment-related activities. The measures listed should allow comparison with other studies
[33] and also overcome some of the shortcomings in previous studies, such as limited estimates of cost-effectiveness. Self-report measures may also limit observer bias, although this may be open to subject bias. The lack of a structured clinical interview (for example, the Eating Disorder Examination) is also a shortcoming, although patients are screened on the basis of meeting criteria for an eating disorder, following an interview with an experienced clinician.

